## **4 Trial procedures**

Patients will all be seen at the Glasgow Clinical Research Facility for all appointments.

Patients randomised to control will be advised to continue with usual care for 3 months before coming back to receive the intervention. They will be asked not to aim to lose any weight during the initial control period, but rather to wait until they commence the intervention part of the study. An appointment will be given to the patient for 3-months' time, and they will commence the intervention at that point.

Patients randomised to intervention will commence Counterweight Plus, which includes a TDR phase followed by structured food reintroduction. This will be delivered by research Dietitians experienced in programme delivery.

**TDR phase (0 to 12-20wks):** A commercial micronutrient-replete 825-853kcal/d LELD will be provided (Cambridge Weight Plan) to replace normal foods, with ample fluids, for 12-20 weeks. Oral hypoglycaemic agents (OHA), antihypertensive and diuretic drugs will be withdrawn on commencement of TDR, and reintroduced (according to guidelines) if diabetes or hypertension returns. Aspirin will be continued in patients prescribed this because of a previous MI (prior to the previous 6 months), but will be discontinued in patients who are prescribed it purely because they have T2D. Beta-blockers will be continued in patients prescribed these for the management of angina. A soluble fibre supplement (Fybogel 2x3.5g/day) will be prescribed to avoid constipation.

Participants will return for review one week after commencement on the TDR and at 2 weekly intervals thereafter till week 12-20 (total of 7-13 appointments) and the commencement of the food reintroduction stage.

To allow some flexibility for patients whose commitments, or practical limitations vary, the TDR phase will be permitted to continue up to 20 weeks if they fail to lose >15kg by week 12. Any patient whose BMI falls below 22 kg/m^2, before week 12 will be moved forward to 'food reintroduction and weight maintenance'. Reasons for moving to food reintroduction prior to week 12 will be recorded.

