| Rationale:           | 
This proposal is for a small pilot study in South Asian patients,, essentially identical to the protocol used by the same research team in the Type 2 diabetes Remission Clinical Trial (DiRECT) study in Caucasian patients, which has now completed recruitment of 290 patients. Published research in people of European origin demonstrates that low/very low energy diets achieving around 15 kg weight loss usually lead to diabetes remission, after 8 weeks of treatment. The Diabetes Remission Clinical Trial (DiRECT) is currently underway in Tyneside and Scotland to assess long-term outcomes of this treatment approach in primary care. However, to date research has not been conducted using this approach with patients of South Asian origin. South Asians are typically diagnosed with Type 2 diabetes 5-10 years younger, with a briefer period of 'prediabetes', and at a lower body mass index than white Europeans. For any given BMI, South Asians have higher fat mass and a larger proportion of fat mass in deep intra-abdominal visceral depots and in ectopic sites: there is emerging evidence for greater liver and pancreas fat, driving type 2 diabetes. This is potentially reversible, but conventional weight management methods commonly achieve less weight loss among South Asians. The proposed study will assess if an existing evidence-based weight management programme, 'Counterweight-Plus', is acceptable to patients of South Asian origin and achieves weight change and reversal of T2DM compared with routine care. The Primary focus being acceptability of TDR in this population and response in terms of weight change and remission of diabetes following the TDR. Initial findings will be used to inform a larger randomised controlled trial.
 |

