|                             | 
At baseline and again after weight loss has been completed and weight stabilized (16-20 weeks), all participants will complete questionnaires on Quality of Life and have blood samples and anthropometric data collected. A questionnaire exploring participant's weight loss expectations and current diet will be administered at baseline.
 
Treatment acceptability will be assessed by questionnaire at the end of the study period
 
Intervention arm, consenting patients will undertake Counterweight-Plus, delivered by a research dietitian. Any existing anti-diabetic, anti-obesity and antihypertensive medications will be withdrawn at the start of 825-853kcal/day 'Total Diet Replacement' liquid diet phase. If necessary they will be reintroduced using standardised protocols according to blood glucose and BP increases. All other management of type 2 diabetes will continue as per clinical guidelines.
 
A questionnaire to quantify psychological process measures (motivation, self-efficacy, resources, self-regulation, habit, satisfaction with outcomes, diet/behaviour, goal conflict, goal facilitation, social support and environmental support) will be completed by participants at each intervention visit
 
An MRI scan will be performed at baseline and repeated after weight loss.
 
Participants will be invited to undergo additional measurements of Metabolic Rate (resting and during physical activity) and Body Composition. These tests will be optional
 
Control arm, patients will continue to be treated according to clinical guidelines.
 |

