| Product, Dose, Modes of Administration: | 
The intervention to be assessed is an 825-853kcal/day TDR, planned to be followed for 12 weeks, with stepped food reintroduction, using a tested energy-restricted nutritionally balanced (30% fat, <10% saturated fat) weight loss maintenance diet using food-group exchanges, plus support to increase physical activities to approach 15,000 steps/day if individually acceptable) with 30 minutes brisk-walking daily. Both intervention and control arms will continue to receive standard care under current clinical guidelines for T2DM. The intervention will be delivered by research dietitians who are trained and competent in Counterweight Plus. Process evaluation will be conducted to assess the number of patients invited, the number who engage with the programme, and completion and attrition rates. Participants will be asked to give written feedback on the programme. Assessments of quality of life, weight loss expectations, and psychological process measures will be made. Mechanistic studies will also be conducted to investigate the changes in pancreatic and liver fat. Participants will be offered the option of undergoing measurements of MR and body composition. These data will inform a larger randomised controlled trial.
 |

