### **1.2 Rationale**

Currently one in every hundred people in Scotland are of South Asian ethnicity and weight management and T2DM are two significant health issues. However evidence suggests sub-optimal engagement and outcomes around weight management for the South Asian population. The cost of diabetic medications in Scotland is currently around £80 million per year and has doubled in the last 10 years, largely related to obesity. Figures therefore would suggest that just short of £1 million per year is spent on diabetic medications for the Scottish South Asian population of around 4500: NB this figure being conservative due to the higher risk of T2DM in the South Asian population. Without appropriate research and development in the South Asian population for this area of care, the cost of the burden of obesity will continue to multiply as well risking an increase in levels of health inequalities for this population. There is overwhelming evidence that modest sustained weight loss, e.g. current target of 5-10% prevents the onset of most new T2DM in people with prediabetes and it improves all aspects of diabetes control (glycaemia, blood pressure, lipids and microvascular damage with reductions in drug doses. Advice to lose and maintain 5-10% weight loss, by diet and exercise is included in most guidelines. However, most T2DM patients are now managed in primary care, many do not see a dietitian, and few achieve 5% weight loss.

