## **3. STUDY DESIGN**

The study will follow a randomised controlled design with patients being randomised to either the weight management intervention or the control group. The control group will be asked to continue following usual management of type 2 diabetes for 3 months, prior to starting the intervention. This study will be performed according to

the Research Governance Framework for Health and Community Care (Second edition, 2006).

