#### **4.1 Study schedule (App A)**

##### **Appointment (Appt) 0: Baseline (All Patients)**

- Review and discuss study participation
- Review inclusion/exclusion criteria including readiness to change screening
- Secure informed consent
- Assign study ID
- Measurement of: height, weight, waist & hip circumference & blood pressure
  - Weight measured using study scales and printout of weight countersigned by practice nurse/dietitian and CW specialist
  - Three blood pressure readings recorded 2-3 minutes apart
  - Waist and hip not measured if BMI>35kg/m^2

Venepuncture for:

- HbA1c, urea and electrolytes, glucose, insulin, liver function tests, lipids.)\*. All Fasting Sample, as per Sample Handling Manual (App C)
- Pregnancy test in women of childbearing years
- Questionnaire completion: EQ-5D, Participant Expectation and Psychological Process Questionnaire
- Randomise patient to CONTROL or INTERVENTION
- Completion of practitioner workbook by research dietitians
- Appointment made for MRI Scan

- Arrange appointment for MR, body composition and appetite hormones measurements if participant has consented to these.
- **INTERVENTION ONLY:** Samples of TDR products given to patients to allow choice of product to be used during intervention to be made.
  - **CONTROL ONLY:** Advised to continue with usual care as per current guidelines. Appointment made for 3 months for repeat
  - measurement of MR, body composition and appetite hormones,
  - MRI scan and venepuncture for HbA1c, urea and electrolytes, glucose, insulin, liver function tests,
  - commencement of weight management intervention

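### Controls are asked not to try to lose weight for 3 months, so the concurrent comparator is deferred weight loss rather than the routine care the protocol names

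*Protocol*

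**What the plan says.** The protocol describes the control arm in several places, nearly always as ordinary care:

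- Study Synopsis, control arm: "patients will continue to be treated according to clinical guidelines".
- Study Synopsis, product and dose row: "Both intervention and control arms will continue to receive standard care under current clinical guidelines for T2DM".
- Section 3: "The control group will be asked to continue following usual management of type 2 diabetes for 3 months".
- Section 4: "Patients randomised to control will be advised to continue with usual care for 3 months".
- Section 4.1, baseline appointment, controls: "Advised to continue with usual care as per current guidelines".

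The synopsis rationale gives the aim as finding out whether the programme "achieves weight change and reversal of T2DM compared with routine care", and section 1.3 repeats the comparison with routine care.

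Section 1.2 says what guideline care contains: "Advice to lose and maintain 5-10% weight loss, by diet and exercise is included in most guidelines".

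Section 4 then adds an instruction for controls that none of the other descriptions carries: "They will be asked not to aim to lose any weight during the initial control period". They are to wait until their own intervention starts.

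**The concern.** Weight loss is one of the main outcomes in section 4.2, and the section 4 instruction acts on it directly, in one arm only. If guideline care includes advice to lose weight, an arm asked not to try is not receiving guideline care in that respect. The randomised 3-month difference then estimates the programme against postponed weight loss, whereas the protocol says it estimates the programme against routine care. HbA1c and MRI fat, which are also collected from controls at the end of the control period, would be expected to move in the same direction as weight.

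Two things are at stake: what the randomised comparison can be said to show, and whether its result can be carried into planning the larger trial as an effect against usual care. There is also a conduct issue. Staff working from section 3, section 4.1 or the synopsis would not know of the instruction, so what controls are told could depend on which section is followed.

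**Working it through.** **Step 1. Set the descriptions side by side.**

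| Place | Control arm described as | Asks controls not to aim to lose weight? |
|---|---|---|
| Synopsis, rationale, and section 1.3 | routine care | no |
| Synopsis, control arm | guideline treatment | no |
| Synopsis, product and dose row | guideline standard care, both arms | no |
| Section 3 | usual management | no |
| Section 4 | usual care | **yes** |
| Section 4.1, baseline appointment | usual care per guidelines | no |
| Section 1.2 (background) | most guidelines advise 5-10% loss | not applicable |

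The section 4 instruction stands alone, and it runs against the content that section 1.2 gives to guideline care.

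**Step 2. Find which stated figures use the concurrent control arm.** Section 6.1 contains two calculations.

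- *Margin for weight change.* Inputs from section 6.1: n = 20, SD 6 kg, stated margin 2.8 kg. A one-sample t interval gives t(0.975, 19) × 6/√20 = 2.093 × 1.342 = 2.81 kg, which reproduces the stated figure. Although the text speaks of a randomised comparison, this margin describes one group of 20 and involves no control mean.
- *Remission.* The combined immediate and delayed groups (n = 20) are compared with 12% in the control group of an external trial. The concurrent controls' first 3 months do not enter.

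Neither figure changes if the control instruction changes.

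**Step 3. Ask how large the shift could be.** The documents give no mean weight loss under routine care, only that few reach 5%. The following is an illustration on assumed values: baseline weight 80-100 kg, and 10-30% of routine-care patients losing 5-10% within 3 months.

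- Low end: 0.10 × 0.05 × 80 kg = 0.4 kg.
- High end: 0.30 × 0.10 × 100 kg = 3.0 kg.

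A smaller share of responders, or an instruction that changes little behaviour, would take the shift towards zero.

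**Step 4. Ask whether the trial could detect such a shift.** Assume the 20 participants split 10 and 10, with SD 6 kg in each arm. The two-arm 95% margin is t(0.975, 18) × 6 × √(1/10 + 1/10) = 2.101 × 2.683 = 5.64 kg. The whole illustrative range lies inside that margin, so the data could neither show nor correct the shift. It has to be handled by how the comparator is described.

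**The case against.** The best defence is that section 4 states a waiting-list design openly: ordinary care continues and new weight-loss attempts are deferred. Section 1.2 is background on what most guidelines contain and does not prescribe what these controls will be told. The study is a feasibility study, and sections 6 and 6.1 rest no quantified analysis on the concurrent controls. Section 1.2 says that few patients achieve 5% loss, and the synopsis says that conventional methods commonly achieve less in South Asian patients, so the instruction may remove very little. Volunteers screened for readiness to change and promised the programme might, if left alone, lose more than ordinary routine-care patients. In that case the instruction could bring them nearer to care as actually delivered.

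Most of this stands as a limit on size and certainty. It does not remove the mismatch of labels: the protocol calls the comparator routine care in its aim, and a deferred-weight-loss arm does not carry that name without qualification.

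A reader might infer more than the documents support:

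- *That the effect is inflated as a fact.* The direction is plausible measured against guideline advice, but routine care as delivered may produce little loss.
- *That the inflation can be expressed as a share of 8 kg.* In section 6.1 the 8 kg is an example of an average observed change in one group. It is not a between-arm difference.
- *That the larger trial will be sized on a biased difference.* The synopsis methodology says the future power calculation draws on the distribution of weight changes once controls have also been offered the intervention. It does not mention the between-arm difference.
- *That participants will certainly receive conflicting advice.* The advice given by general practices and the participant materials are not shown.

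**Conclusion.** The concern holds as a matter of comparator definition and interpretation. Section 4 makes the concurrent control a deferred-weight-loss arm, while the synopsis and sections 1.3, 3 and 4.1 name it routine, usual or guideline care. Any randomised 3-month difference in weight, HbA1c or MRI fat may overstate the effect against routine care. The size is unknown and may be small. The 0.4-3.0 kg illustration rests wholly on assumed baseline weights and responder shares, and values nearer zero are compatible with the text. The external-control remission test and the 2.8 kg margin are untouched, as is the acceptability objective.

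**What to change.** Reconcile section 4 with the synopsis (rationale, control arm, product and dose row) and sections 1.2, 1.3, 3 and 4.1, so that one statement of what controls are asked to do appears throughout. Which instruction to use is for the investigators to decide.

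- If the instruction stays, describe the comparator as deferred treatment with participants asked not to attempt weight loss. Remove the comparison with routine care from the synopsis rationale and section 1.3. State that the between-arm difference will not be interpreted, or used in planning the larger trial, as an effect against usual care.
- If the instruction is withdrawn, the existing descriptions of the control arm can stand.

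Either route is a short wording amendment with matching participant wording. It adds no visits, measurements or participants.

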### **3.3 Exclusion criteria**

- Current insulin use
- Recent routine HbA1c on record  $\geq 12\%$
- Weight loss of  $>5\text{kg}$  within the last 6 months
- Recent eGFR on record  $<30 \text{ mls/min/1.73}^2$
- Substance abuse
- Known cancer
- Myocardial infarction within previous 6 months
- Severe or unstable Heart Failure defined as equivalent to the New York Heart Association (NYHA):
  - Grade 3 - marked limitation of physical activity. Comfortable at rest, but less than ordinary activity causes fatigue, palpitation, or breathlessness, and
  - Grade 4 - unable to carry out any physical activity without discomfort. Symptoms of cardiac insufficiency at rest. If any physical activity is undertaken, discomfort is increased.
- or**
- Grade 2 if symptoms are not attributed to obesity - Slight limitation of physical activity. Comfortable at rest, but ordinary physical activity results in fatigue, palpitation, or breathlessness
- Learning difficulties
- Not fluent in English language
- Current treatment with anti-obesity drugs
- Diagnosed eating disorder or purging
- Pregnant/ considering pregnancy

- Patients who have required hospitalisation for depression or are on antipsychotic drugs
- People currently participating in another clinical research trial
- People with metal implants or devices and those who have claustrophobia cannot take part as MR scans are needed as part of the study

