### **Appt 1: Week 0+1**

#### **Intervention Participants**

- Measurement of weight, blood pressure and capillary blood glucose (measured by blood glucose meter) recorded
- Oral hypoglycaemic, antihypertensive and diuretic medications discontinued
  - Aspirin only discontinued in patients who are prescribed it purely because they have T2D.
  - Beta-blockers continued in patients prescribed these for the management of angina.
- Commence TDR phase of intervention as per Counterweight Plus Appointment Planner (App C)
  - Fybogel supplement prescribed
- Appointment made for next visit

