## APPENDIX A: STANDby SCHEDULE OF ASSESSMENTS

| APPENDIX 1: STANDARD SCHEDULE OF ASSESSMENTS |                   |                              |          |          |          |          |           |           |                           |           |            |            |
|----------------------------------------------|-------------------|------------------------------|----------|----------|----------|----------|-----------|-----------|---------------------------|-----------|------------|------------|
| Appointment
Week                          | 0
0 (Baseline) | Total Diet Replacement Phase |          |          |          |          |           |           | Food Reintroduction Phase |           |            |            |
|                                              |                   | 1
0+1                     | 2
0+2 | 3
0+4 | 4
0+6 | 5
0+8 | 6
0+10 | 7
0+12 | 8
0+13                 | 9
0+15 | 10
0+17 | 11
0+19 |
| Study Procedure                              |                   |                              |          |          |          |          |           |           |                           |           |            |            |
| Review & discuss study participation         | √ a    |                              |          |          |          |          |           |           |                           |           |            |            |
| Review Inclusion/Exclusion Criteria          | √ a    |                              |          |          |          |          |           |           |                           |           |            |            |
| Obtain Informed Consent                      | √ a    |                              |          |          |          |          |           |           |                           |           |            |            |
| Height                                       | √ a    |                              |          |          |          |          |           |           |                           |           |            |            |
| Weight                                       | √                 | √                            | √        | √        | √        | √        | √         | √         | √                         | √         | √          | √          |

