| MR Measurements b                 | √                 |                              |          |          |          |          |           |           | √                         |           |            | √          |
| Body Composition Measurements b   | √                 |                              |          |          |          |          |           |           | √                         |           |            | √          |
| Appetite hormones b               | √                 |                              |          |          |          |          |           |           | √                         |           |            | √          |

a initial visit only

b optional measurements

c Control participants only – Bloods, MRI scan & optional measurements repeated at end of control period

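### Controls start total diet replacement about 3 months after the only scheduled eligibility review and pregnancy test, and no written rule makes that start conditional on the safety exclusions

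*Protocol*

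**What the plan says.** Section 3.3 of the Protocol lists exclusions that can change with time, among them "Pregnant/ considering pregnancy" and "Myocardial infarction within previous 6 months", as well as heart failure, known cancer, insulin use and eGFR below 30.

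Section 4.1 places the review of these criteria at Appointment 0, before randomisation. The same visit carries "Pregnancy test in women of childbearing years". In Appendix A the row "Review Inclusion/Exclusion Criteria" has a single tick at week 0, with a footnote that reads "initial visit only". Appendix A has no row for a pregnancy test.

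Under section 4, controls continue usual care for 3 months and are then given an appointment, "and they will commence the intervention at that point". For the end of that period, Appendix A specifies "Bloods, MRI scan & optional measurements repeated at end of control period". Section 4.1 names the same items (HbA1c, urea and electrolytes, glucose, insulin and liver function tests, plus MRI and optional tests) and then lists the start of the intervention.

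At Appointment 1, weight, blood pressure and capillary glucose are measured, the instruction is "Oral hypoglycaemic, antihypertensive and diuretic medications discontinued", and TDR begins. No eligibility step is listed there or in the Appointment 1 planner.

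**The concern.** The exclusions protect people who are about to spend 12-20 weeks on 825-853 kcal/day with several classes of drug withdrawn. They should therefore describe the participant when that exposure starts. In the immediate arm they do. In the delayed arm they describe the participant as she or he was about 3 months earlier.

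Followed as written, the schedule would let a control who has become pregnant during the wait, or who has newly met another safety exclusion, start TDR. What is at stake is participant safety. The randomised 3-month comparison is complete by then, and its estimates are not affected.

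**Working it through.** The plan gives no figure to reproduce. The check sets the schedule of the two arms side by side, with some simple arithmetic on timing.

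| Step | Immediate arm | Delayed arm (controls) | Source |
|---|---|---|---|
| Eligibility review | Appointment 0 | Appointment 0 only | 4.1; Appendix A, footnote a |
| Pregnancy test | Appointment 0 | Appointment 0 only | 4.1 |
| Checks at end of control period | not applicable | bloods, MRI, optional tests; no threshold attached | 4.1; Appendix A, footnote c |
| TDR start and drug withdrawal | Appointment 1, week 0+1 | appointment at 3 months | 4; 4.1 |
| Rule for not starting | none needed so soon after review | none stated | 3.5, 4, 4.1, 5 |

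**Age of the checks at TDR start.** Immediate arm: about 1 week, taking Appointment 1 (week 0+1) as the start. Delayed arm: 3 months, or about 13 weeks. Difference: 13 − 1 = about 12 weeks.

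**Age of the pregnancy test at the end of TDR.** TDR lasts 12-20 weeks. Delayed arm: 13 + 12 = 25 to 13 + 20 = 33 weeks. Immediate arm: 1 + 12 = 13 to 1 + 20 = 21 weeks.

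**Myocardial infarction.** The exclusion looks back 6 months and the wait is 3 months. Because 6 > 3, any infarction during the wait is still within the exclusion window on the day TDR starts.

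**How many are exposed to the gap.** The protocol text shown does not give the allocation ratio. Assuming 1:1, 25 / 2 gives 12 or 13 controls, all affected by the missing eligibility review. The missing pregnancy test concerns only the women of childbearing years among them, whose number is not given.

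**What other text could close the gap.**
- Section 4's aspirin rule requires staff to know about a previous infarction and uses the same 6-month limit.
- Urea and electrolytes and HbA1c are repeated at 3 months, so falling renal function or very poor control could be noticed.
- Section 5 (the text under its Appendix E heading) has results that may pose a risk discussed with the patient and the GP.
- Section 9 asks about adverse events at each study visit, and Appendix F records medical contacts and hospitalisations since the last appointment.
- The synopsis says that controls are offered the intervention.

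Together these would probably bring an infarction or a low eGFR to light. None says that TDR must not start, and none would detect a pregnancy.

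**The case against.** The best case for the plan is that more is checked at TDR start than the schedule suggests. Staff must go through each participant's oral hypoglycaemic, antihypertensive and diuretic drugs and the reason for any aspirin or beta-blocker, which would tend to reveal new insulin use as well. For a control, the record of medical contacts since the last appointment spans the whole wait, so a hospital admission for infarction or heart failure, or a new cancer diagnosis, should surface. The wording about commencing at 3 months can be read as scheduling, not as an order to start despite a known contraindication. Appendix A is visibly incomplete, since it omits even the Appointment 0 pregnancy test, so its silence proves little. The flow chart is not shown, and patient information could carry advice on pregnancy. Women considering pregnancy are already excluded. Neither arm has a repeat test during TDR, so the matter could be seen as a choice of how often to test.

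Much of this stands as mitigation: for most exclusions a clinician would probably find out. It does not remove the point. Becoming aware of an event is not the same as a rule against starting. Appendix A does more than stay silent, because it confines the review to the first visit, and the text of section 4.1 agrees with it. An offer concerns the participant's choice, not eligibility. Pregnancy remains undetected by any scheduled step. The absence of testing during TDR is common to both arms; the point here is that one arm is checked shortly before exposure and the other is not.

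**Conclusion.** The concern holds. The delayed arm would begin the same intervention on an eligibility review and pregnancy test about 13 weeks old, against about 1 week in the immediate arm, and nothing in the protocol makes the start conditional on the safety exclusions still being absent.

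The eligibility gap affects all controls, 12 or 13 people under an assumed 1:1 allocation; the pregnancy gap affects an unstated number of women among them. How many would newly meet an exclusion cannot be derived from the document and is probably small. The point should be fixed because the potential harm is to participants and the remedy is cheap. It does not bias any estimate. The 1-week figure rests on reading Appointment 1 as the start of TDR, as section 4.1 states.

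**What to change.** In section 4.1 and Appendix A, add for controls at the end-of-control visit, before TDR starts and drugs are withdrawn:

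1. a repeat review of the existing safety exclusions (pregnancy, infarction within 6 months, heart failure, cancer, insulin use, eGFR below 30);
2. a repeat pregnancy test in women of childbearing years;
3. sight of the end-of-control blood results, which are already planned.

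State that a control who newly meets a safety exclusion does not start TDR but remains in the randomised 3-month comparison.

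The cost is a short amendment, one inexpensive test where applicable and a short delay while results are seen. One or two fewer participants might start the delayed intervention: 1/25 = 4% or 2/25 = 8% of the sample. Section 6.1 already anticipates about 25% not completing (0.25 × 25 = 6.25, about 6 people).
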